#### Statistical analysis plan.

Data will be analysed on an intention-to-treat basis. Baseline demographics, obstetric history, and pregnancy-related variables will be summarised by treatment arm using means and standard deviations (or medians and interquartile ranges) for continuous variables and frequencies and percentages for categorical variables. Between-group balance will be described using standardised mean differences (SMD); formal significance testing of baseline differences will not be performed, consistent with established guidance for randomised trials [11]. Two time intervals will be recorded for every woman who reaches the second stage of labour:(i) the duration of the active pushing phase, defined as the interval in minutes from the first coordinated maternal expulsive effort accompanying a uterine contraction, whether spontaneous or initiated following midwifery coaching, until delivery;(ii) the duration of the total second stage, defined as the interval in minutes from confirmed full cervical dilatation until delivery. The duration of the active pushing phase is the primary endpoint, referred to throughout as the duration of active second stage of labour**,** as it corresponds to the phase targeted by the intervention and to the phase in which levator ani co-activation has been shown to operate [2,3], and is the interval from which the assumed standard deviation used in the sample size calculation was derived. The duration of the total second stage is reported as a secondary endpoint. Both intervals are recorded contemporaneously in the electronic partogram and extracted for analusis by a researched blinded to allocation.

The primary endpoint will be analysed using multivariable linear regression, with treatment arm as the main predictor. The model will be adjusted for pre-specified baseline covariates only, that is, variables measured before randomisation: maternal age, body mass index at enrolment, gestational age at randomisation, maternal height, and sonographic estimated fetal weight at the last available third-trimester scan. Consistent with ICH E9, no post-randomisation variable is included in the confirmatory model, since conditioning on variables measured after allocation may invalidate the randomisation-based causal interpretation of the treatment effect. This applies in particular to fetal head position at full cervical dilatation, epidural analgesia and gestational age at delivery, which are potential intermediate variables on the causal pathway between the intervention and the primary endpoint. Their distribution across arms will be reported descriptively, and epidural analgesia and fetal head position will be examined as potential effect modifiers through interaction terms, as exploratory analyses. The primary result will be reported as an adjusted mean difference with 95% confidence interval; the p-value will be provided as secondary inferential information. If the residuals of the linear model indicate substantial departure from normality, a bootstrap confidence interval will be computed. Women who do not reach the active second stage (e.g., caesarean delivery before full dilatation) will not contribute to the primary analysis but will be retained in the ITT population for all secondary outcomes. For clarity, the primary estimand may therefore be summarised as the difference in adjusted mean duration of the active pushing phase between arms among randomised nulliparous women reaching the active second stage, with operative vaginal delivery and second-stage caesarean section handled under a treatment-policy strategy as delivery events at the observed time. The number of women contributing to each analysis, with the corresponding denominators and reasons for non-contribution, will be reported by arm in the CONSORT flow diagram, and the baseline characteristics of women not reaching the active second stage will be compared between arms using standardised mean differences. Sensitivity analyses will include multiple imputation under the missing-at-random assumption and inverse probability weighting to assess the robustness of the primary estimate to differential attrition, applied to observations that are missing rather than undefined, such as incomplete partogram times or non-returned questionnaires; where an imbalance is observed in the proportion of women reaching the active second stage, inverse probability of selection weights will be applied accordingly. Time to spontaneous vaginal birth from the onset of active pushing will additionally be described using cumulative incidence functions, with operative vaginal delivery and second-stage caesarean section treated as competing events rather than as censored observations, and compared between arms using Gray's test. This analysis is supportive and exploratory.

Mode of delivery (spontaneous vaginal birth vs. operative vaginal or caesarean), perineal tears (≥ 3rd degree vs. none/1st–2nd degree), postpartum haemorrhage (≥ 500 mL vs. < 500 mL), and need for pharmacological augmentation during the active second stage will be analysed using logistic regression with the same set of pre-specified baseline covariates. Results will be reported as adjusted odds ratios with 95% CIs, accompanied by absolute risks and risk differences by arm to facilitate clinical interpretation. For endpoints with a low expected number of events, Firth's penalised-likelihood estimation will be used. Third- and fourth-degree perineal tears will be analysed among all women reaching the second stage, with caesarean deliveries counted as no injury, and additionally among women delivering vaginally. Mode of delivery is also addressed within the competing-risks analysis described above. Total postpartum blood loss (mL) and maternal satisfaction (CEQ-2 score) will be analysed using multivariable linear regression as described for the primary endpoint, reporting adjusted mean differences with 95% CIs, with bootstrap confidence intervals reported for blood loss in view of its expected skewness. Urinary incontinence (ICIQ-SF score ≥ 6) will be assessed at 6 weeks, 12 weeks and16 weeks postpartum. The outcome will be modelled using mixed-effects logistic regression with a random intercept for participant and fixed effects for treatment arm, time point, and their interaction, adjusted for the same baseline covariates. This approach accounts for within-subject correlation across repeated assessments and allows estimation of the treatment effect trajectory over time and makes use of all available observations under a missing-at-random assumption. Both the interaction term and the adjusted treatment effect at each time point will be reported. Attendance at postpartum pelvic floor rehabilitation, a post-randomisation variable, will be summarised descriptively by arm and, where uptake exceeds 10% in either arm, included in sensitivity analyses for pelvic floor–related outcomes as described above. Pre-specified subgroup analyses will examine potential effect modification by: (i) Within-arm analysis of levator ani function (intervention arm only); (ii) gestational age at intervention (28–34 weeks vs. 35–37 weeks); and (iii) epidural analgesia (yes/no). Subgroup (ii) and subgorup (iii) are defined by post-randomisation variables and are reported as exploratory only. Subgroup effects will be estimated via interaction terms in the regression models and reported as stratum-specific effect estimates with 95% CIs. All secondary, subgroup, and repeated-measures analyses are regarded as exploratory and hypothesis-generating. The trial is powered exclusively on the primary endpoint. Results of secondary analyses will be reported as point estimates with 95% confidence intervals without correction for multiplicity and should be interpreted in the context of the overall pattern of findings rather than as confirmatory evidence. All analyses will be conducted using R (R Foundation for Statistical Computing) and STATA (StataCorp LLC).

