To quantify the proportion of women who demonstrate levator ani muscle (LAM) co-activation—defined as an anteroposterior diameter change (APD) < 0 mm—at two time-points: (i) during the TPUS-guided training session, and (ii) at birth, where an intrapartum sonographic assessment is feasible within routine clinical care.To compare postpartum maternal satisfaction between the control and TPUS-guided intervention arms, as measured by the Childbirth Experience Questionnaire 2 (score range 0–100).To quantify the difference of prevalence in 1st-, 2nd-, 3rd- and 4th-degree perineal tears between the control and the TPUS-guided intervention arms.To measure the difference in total postpartum blood loss (mL) within 24 hours of delivery between the control and the TPUS-guided intervention arms.To compare the rates of spontaneous vaginal birth, operative vaginal birth and unplanned caesarean sections between the control and the TPUS-guided intervention arms.To evaluate the prevalence of stress or urge urinary incontinence at 6, 12, 16 weeks postpartum between the control and the TPUS-guided intervention arms, defined as an International Consultation on Incontinence Questionnaire-Urinary Incontinence Short Form (ICIQ-SF) score ≥ 6.To compare the proportion of women that require pharmacological augmentation during the active second-stage of labour between the control and TPUS-guided intervention arms.To quantify the association between persistent fetal malposition (non-occiput-anterior at full cervical dilatation and/or at delivery) and the length of the second stage of labour (minutes), and to test whether this association differs between the control and TPUS-guided intervention arms. This association is observational in nature and is not interpreted as a randomised comparison.

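### Women delivered by caesarean before full dilatation are kept for every secondary outcome by one rule and dropped from the severe-tear analyses by another, so caesareans are scored differently by timing

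*Protocol article*

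**What the plan says.** All the relevant text is in the protocol article, mostly under Statistical analysis plan.

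- **General rule (primary-endpoint paragraph).** Women not reaching the active second stage, with caesarean before full dilatation as the example given, "will not contribute to the primary analysis but will be retained in the ITT population for all secondary outcomes".
- **Severe tears (secondary-outcomes paragraph).** "Third- and fourth-degree perineal tears will be analysed among all women reaching the second stage, with caesarean deliveries counted as no injury". The same sentence then names a further analysis set: "and additionally among women delivering vaginally". Tears belong to the secondary objectives: "To quantify the difference of prevalence in 1st-, 2nd-, 3rd- and 4th-degree perineal tears between the control and the TPUS-guided intervention arms". The binary secondary outcomes are to be reported as adjusted odds ratios with absolute risks and risk differences by arm.
- **Second-stage duration.** "The duration of the total second stage is reported as a secondary endpoint". It runs from confirmed full dilatation, and "Two time intervals will be recorded for every woman who reaches the second stage of labour".
- **Augmentation.** The "need for pharmacological augmentation during the active second stage will be analysed using logistic regression". No denominator is given for women without an active second stage.
- **Disclosure.** For the CONSORT diagram the plan promises: "The number of women contributing to each analysis, with the corresponding denominators and reasons for non-contribution, will be reported by arm".

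**The concern.** The general rule admits no exception, yet the tear rule makes one. Take two randomised women, both delivered by caesarean and neither with a perineal tear. The one operated on after full dilatation enters the tear analysis as a non-event. The one operated on earlier leaves it. Nothing about the injury differs between them, only the timing of the operation.

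Reaching the second stage happens after randomisation. The plan is alert to this elsewhere: it keeps post-randomisation variables out of the confirmatory model, and it provides selection weights for the primary estimate if the arms differ in the proportion reaching the active second stage. The tear analysis has no comparable protection and does not need the restriction, because the plan's own coding supplies a value for every caesarean.

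At stake are the severe-tear risks and risk difference, which change with the denominator, and the freedom to choose between two written rules once the data are seen.

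**Working it through.** **1. The rules side by side**

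| Woman | General retention rule | Main tear rule | Vaginal-birth tear analysis |
|---|---|---|---|
| Vaginal birth | in | in, as observed | in |
| Caesarean after full dilatation | in | in, no injury | out |
| Caesarean before full dilatation | in | **out** | out |

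The last row is the contradiction. There is also a smaller mismatch: the retention rule refers to the active second stage and the tear rule to the second stage. A woman fully dilated but delivered before pushing is thus outside the primary analysis and inside the tear analysis.

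**2. Inputs for the size**

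- 134 women per arm (Sample size). This agrees with the plan's own steps: 114 / 0.85 = 134.1.
- Caesarean rate 19% (Setting). This is the hospital's primary caesarean rate for 2025; no split by parity or timing is given, so using it for the trial population is an assumption.
- Share of caesareans before the second stage: not given; varied from 0 to 100%.
- Severe-tear risk per vaginal birth: not given; 3% assumed.

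**3. Denominators per arm**

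- Caesareans: 0.19 × 134 = 25.5. Vaginal births: 134 − 25.5 = 108.5.
- Severe tears: 0.03 × 108.5 = 3.26 events.
- Women reaching the second stage: 134 − f × 25.5, where f is the share of caesareans before it.

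| f | Women reaching second stage | Risk under the main tear rule | Risk, all randomised | Risk, vaginal births |
|---|---|---|---|---|
| 0 | 134.0 | 2.43% | 2.43% | 3.00% |
| 0.25 | 127.6 | 2.55% | 2.43% | 3.00% |
| 0.50 | 121.3 | 2.69% | 2.43% | 3.00% |
| 0.75 | 114.9 | 2.83% | 2.43% | 3.00% |
| 1 | 108.5 | 3.00% | 2.43% | 3.00% |

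**4. Apparent difference from timing alone**

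Let both arms have the same injuries and the same number of caesareans, differing only in f.

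- f = 0.75 against 0.25: 2.83% − 2.55% = 0.28 percentage points.
- f = 1 against 0: 3.00% − 2.43% = 0.57 percentage points.
- All randomised as denominator: 2.43% − 2.43% = 0.

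**5. Against sampling error**

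With a risk of 2.43% and 134 per arm, the half-width of a 95% interval for the risk difference is about 1.96 × √(2 × 0.0243 × 0.9757 / 134) = 1.96 × 0.0188 = 0.037, or 3.7 points (a normal approximation, rough with about three events per arm). The distortion is well inside that.

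**The case against.** The strongest reply is that the specific rule governs the general one. The retention sentence describes who stays in the ITT population, the tear sentence sets the denominator for tears, and an analyst would follow the latter. The plan also adds a vaginal-birth analysis, promises denominators and reasons for non-contribution by arm, and labels all secondary analyses exploratory. Restricting to women who reach the second stage limits structural zeros. Counting every caesarean as no injury would in turn favour an arm with more early caesareans.

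Much of this stands. The consequence is small, and the denominator used would be visible in the report. The choice of denominator is partly a choice of estimand, and the all-randomised version must be read beside mode of birth and the vaginal-birth result. What does not stand is that the specific rule settles the matter. The retention sentence says all, without exception, and reporting a denominator afterwards does not fix it beforehand. Nor does an at-risk argument explain the chosen set, which already includes second-stage caesareans as non-events; the vaginal-birth analysis serves that question.

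A reader might infer that the same conflict distorts other secondary outcomes. The documents do not support that. Total second-stage duration is recorded only for women who reach the second stage, so two analysts would use the same women; only the word all is too wide. For augmentation, nothing says that women without an active second stage are coded as not augmented, and no augmentation rate is given from which to size an effect. Whether to count them is a choice of estimand that needs stating, not a demonstrated bias.

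**Conclusion.** The contradiction holds for third- and fourth-degree tears: the retention rule and the tear rule cannot both be applied to women with a caesarean before full dilatation, and the tear rule conditions on a post-randomisation event although a no-injury value is available for every caesarean. For second-stage duration and augmentation, the point is only that the retention sentence is worded too broadly and one denominator is unnamed.

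The size is modest: 0.28 to 0.57 percentage points of spurious difference for severe tears in the scenarios shown, resting on the assumed 3% risk, the hospital-wide 19% rate and marked differences in timing between arms. If timing is balanced, the arms are compared fairly and only the absolute risk shifts, between 2.43% and 3.00%. It would be wrong to infer any threat to the trial's main conclusion, because the primary estimand, its analysis and the sample size do not depend on these rules. It should be corrected because it is a conflict in stated rules and is easily removed.

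**What to change.** In the Statistical analysis plan section:

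1. **Severe tears.** Make the main analysis all randomised women with delivery data, counting every caesarean, whenever performed, as no injury. Keep the analyses among women reaching the second stage and among vaginal births as supportive.
2. **Retention sentence.** Limit it to secondary outcomes defined for every randomised woman: mode of birth, blood loss and postpartum haemorrhage, severe tears, CEQ-2 and urinary incontinence. State that total second-stage duration is analysed among women reaching full dilatation.
3. **Augmentation.** Name one denominator, for example women reaching the active second stage, with the number not reaching it shown by arm.

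The cost is wording and one more tear analysis. Mode of birth and tears are already to be extracted from medical records (Data collections), so no new data are needed. The downside is a slightly lower absolute severe-tear risk in the main analysis, 2.43% rather than 2.69% in the illustration with half of caesareans before the second stage.

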### Randomization, blinding and treatment allocation

Once eligibility is confirmed and informed consent is obtained, participants will be randomised (1:1) into one of two study arms: using a computer-generated random sequence (“randomizeR” package in R**).** Assignment to study groups will be managed through sealed, opaque and sequentially numbered envelopes accessible only to the research midwife, thereby maintaining allocation concealment until the moment of assignment.

Given the nature of the interventions, this study is designed as an open-label trial; both the participants and the researchers will be aware of the group assignments. While full blinding is not feasible due to the involvement of TPUS in one arm, outcome assessors will be blinded to group allocation when evaluating outcomes and analysing data. This approach aims to reduce assessment bias and ensure that the treatment allocation does not influence the collection and interpretation of results.

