### Sample size

The sample size was calculated to detect a mean reduction of 20 minutes in the duration of the active second stage of labour in the experimental group compared with the control group. Twenty minutes was pre-specified as the minimal clinically important difference for the duration of the active pushing phase, rather than as the anticipated magnitude of the treatment effect. Its clinical relevance is anchored to preliminary data showing that nulliparous women with LAM co-activation experience a longer second stage than those without co-activation (83 ± 63 vs. 63 ± 42 minutes, respectively). The pooled standard deviation is 53.5 minutes, yielding a standardised effect size (Cohen’s d) of 0.37, corresponding to a small-to-medium effect consistent with published trials of intrapartum ultrasound-based biofeedback interventions which were delivered intrapartum rather than antenatally. Using a two-sided independent-samples test with α = 0.05 and 80% power, the required sample size is 114 participants per arm (228 total). To account for an anticipated 15% attrition rate, encompassing study dropout, caesarean delivery before or during labour, and operative vaginal delivery precluding assessment of the primary endpoint, the final enrolment target has been set at 268 participants (134 per arm). We acknowledge that the hypothesised effect size assumes a biologically plausible benefit across the entire intervention group. Because preliminary data suggest that approximately 25% of nulliparous women exhibit LAM co-activation, the treatment effect may be attenuated in the overall population if benefit is concentrated in this subgroup. A pre-specified within-arm analysis by co-activation status at training is planned to explore this hypothesis (see Statistical Analysis Plan).

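### The sensitivity analyses named for differential attrition both assume ignorable missingness, so their agreement cannot show robustness to loss that depends on the unrecorded pushing time itself

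*Protocol article*

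**What the plan says.** The section on statistical analysis in the protocol article fits the primary model, a linear regression on arm and five baseline covariates, in women who reach the active second stage. Its sensitivity analyses comprise "multiple imputation under the missing-at-random assumption and inverse probability weighting to assess the robustness of the primary estimate to differential attrition". Their scope is limited: they are "applied to observations that are missing rather than undefined, such as incomplete partogram times or non-returned questionnaires". Women who never reach the active second stage fall outside this scope. For them the plan has separate selection weights, used only if the arms differ in the proportion reaching that stage.

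Three further points bear on the issue:

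- Missing at random is stated for the imputation. For the weighting it is not stated, but it follows from the method.
- The variables in the imputation and weight models are not listed. Post-randomisation variables are barred from the confirmatory model only.
- The Sample size section allows for an "anticipated 15% attrition rate, encompassing study dropout, caesarean delivery before or during labour, and operative vaginal delivery precluding assessment of the primary endpoint".

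**The concern.** The purpose stated for the two analyses is robustness to differential attrition. The kind of attrition that neither the primary regression nor these two analyses can correct is loss that depends, differently by arm, on the duration that was not recorded. Examples would be start-of-pushing times left blank in very long or very hurried births, or women who planned to deliver at the centre but gave birth elsewhere. The trial is open-label, and the endpoint needs a start time charted during labour, so such loss cannot be ruled out.

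Imputation under missing at random and weights built from recorded data do not vary the assumption in question. The risk lies in the interpretation. If the three estimates agree, the report could present this as robustness to differential attrition, although they could agree just as closely when the estimate is biased.

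**Working it through.** **Design figures.** From the Sample size section: difference 20 minutes, two-sided α 0.05, power 80%, and "The pooled standard deviation is 53.5 minutes, yielding a standardised effect size (Cohen’s d) of 0.37".

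- Pooled SD = √((63² + 42²)/2) = 53.54, as stated.
- n per arm = 2(1.960 + 0.842)² × 53.5²/20² = 112.3, so 113 by the normal formula. The t-test version gives 113.3, so 114, which reproduces the plan's figure.
- Standard error at 114 per arm = 53.5 × √(2/114) = 7.09 minutes.

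**Do imputation and weighting depart from the primary estimate?** This was simulated with 1,000,000 women, a true effect of about -20 minutes, a linear primary model, one imputation draw and logistic weights. All missingness mechanisms are assumed; none comes from the documents. Estimates in minutes:

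| Missingness depends on | Variables in imputation and weight models | Full data | Primary regression | Imputation | Weighting |
|---|---|---|---|---|---|
| Arm and baseline covariate (13% vs 20% missing) | baseline only | -19.95 | -19.93 | -19.97 | -19.95 |
| Arm and a recorded post-randomisation variable (4% vs 18%) | baseline only | -19.90 | -21.79 | -21.78 | -21.79 |
| As above | baseline plus that variable | -20.10 | -21.96 | -20.07 | -20.07 |
| The duration itself, intervention arm (about 9% per arm) | baseline only | -19.97 | -23.52 | -23.52 | -23.53 |
| As above | baseline plus a recorded variable | -19.97 | -23.52 | -23.13 | -23.12 |

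With baseline covariates only, the three analyses agree whether the estimate is right (row 1) or wrong (rows 2 and 4). With the relevant recorded variable they expose and remove the bias in row 3. In row 5 most of the bias remains.

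**Size in general.** Let m be the share of times missing in one arm, and δ the amount by which the mean of the missing women differs from what missing at random predicts. Then the shift in the estimate = m × δ. Both inputs are assumed:

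| m | δ = 20 | δ = 40 | δ = 60 |
|---|---|---|---|
| 5% | 1.0 | 2.0 | 3.0 |
| 10% | 2.0 | 4.0 | 6.0 |
| 15% | 3.0 | 6.0 | 9.0 |

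The fourth row of the simulation fits this: its bias of 23.52 - 19.97 = 3.55 minutes with 8.8% missing in the intervention arm corresponds to δ of about 3.55/0.088 = 40 minutes.

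**When would the conclusion change?** Holding the standard error fixed, significance is lost at δ = (|estimate| - 1.96 × 7.09)/m.

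- Observed -20 (95% CI -33.9 to -6.1): 6.11/0.05 = 122 minutes at 5% missing, 61 at 10%, 41 at 15%.
- Observed -15 (95% CI -28.9 to -1.1): 1.11/0.05 = 22 minutes at 5% missing, 11 at 10%.

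An estimate at the design difference is hard to overturn. One near the edge of significance is not. Neither planned analysis would tell the reader which situation applies.

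**The case against.** A reader might infer that the two analyses reproduce every attrition bias and can never reveal one. The documents do not support that. The imputation and weight models may contain recorded post-randomisation variables, and the simulation shows that these can expose bias which the primary regression misses. Nor do the analyses necessarily share the primary regression's assumption: missing at random given a richer set of recorded data is weaker.

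One strong auxiliary is already planned. Total second-stage duration is recorded for every woman who reaches that stage, and it can survive when only the start of pushing is missing. Under an assumed mechanism with no true effect (intervention arm: 27% missing above the 70th percentile of duration and 3% below; control arm: 2%), imputation with such an auxiliary reduces a false effect from -4.6 to -1.6 minutes if its correlation with pushing time is 0.82, but only from -4.6 to -4.3 if it is 0.26. The correlation in this population is not given.

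Other points limit the problem:

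- Times are charted contemporaneously and extracted by a blinded researcher, and the training midwives do not attend the births.
- Much of the 15% allowance is caesarean or operative birth. Women not reaching the active second stage are outside the estimand, and operative births count at their observed time, so the truly missing share is probably well below 15%.
- The list of sensitivity analyses is not worded as exhaustive, and a full analysis plan may hold more. The unlisted model variables are ordinary detail for such a plan and are not faulted here.

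All of this stands, and it narrows the point. It does not remove it: the article names the methods and the purpose they serve, and for loss that depends on the unrecorded duration they cannot serve it.

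**Conclusion.** The concern holds in a limited form. Every analysis named for differential attrition assumes ignorable missingness. With the primary model's covariates alone, imputation and weighting nearly repeat the primary result. With recorded auxiliaries they may correct part of a bias, but they still do not test dependence on the unobserved duration. Their agreement alone therefore does not support robustness to that kind of loss.

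The expected impact is modest: about 2 to 4 minutes at 5 to 10% missing in one arm and a 40-minute departure, against a 20-minute minimal important difference and a standard error of about 7 minutes. The missing shares, the departures and the simulated mechanisms are assumptions. The documents neither show that such loss will occur nor give its rate, so the primary estimate cannot be called biased on this ground. This is an inexpensive improvement to the plan and not a flaw that endangers the trial.

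**What to change.** 1. Keep the imputation and the weighting, and describe both as checks under missing at random.
2. Include recorded auxiliaries in the imputation and weight models, for example total second-stage duration, epidural analgesia and mode of birth. The confirmatory model stays on baseline covariates.
3. Add a delta-adjusted imputation: shift the imputed pushing durations by fixed amounts, for example -40 to +40 minutes in steps of 10, varied separately by arm. Report the shift at which the primary confidence interval changes its conclusion, together with the number of missing times per arm. If no shift in that range changes the conclusion, say so.

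The cost is a sentence or two in the plan, a short loop around an imputation that is already planned, and one more result to report. No new data are needed.

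### The selection-weighted sensitivity analysis should be run in every case, not only when the proportions reaching the active second stage are seen to differ

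*Protocol article*

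**What the plan says.** All of the relevant text is in the Protocol article, under the heading Statistical analysis plan.

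- **Analysis set.** Women who do not reach the active second stage "will not contribute to the primary analysis but will be retained in the ITT population for all secondary outcomes". The estimand is accordingly the adjusted mean difference in pushing time "among randomised nulliparous women reaching the active second stage".
- **Missing data.** "Sensitivity analyses will include multiple imputation under the missing-at-random assumption and inverse probability weighting to assess the robustness of the primary estimate to differential attrition", and these methods are "applied to observations that are missing rather than undefined, such as incomplete partogram times or non-returned questionnaires".
- **Selection.** After a semicolon in the same sentence: "where an imbalance is observed in the proportion of women reaching the active second stage, inverse probability of selection weights will be applied accordingly". No size of imbalance is given, and nothing says that the weights are used otherwise.
- **Description.** Denominators and reasons for non-contribution are reported by arm, and "the baseline characteristics of women not reaching the active second stage will be compared between arms using standardised mean differences". This comparison is unconditional, but it is not linked to the use of the weights.
- **Adjustment.** The confirmatory model always includes maternal age, body mass index, gestational age at randomisation, height and estimated fetal weight.

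**The concern.** Restricting a comparison to women who pass a post-randomisation event can bias it if different kinds of women pass in each arm and those differences predict duration. What matters is who is selected, not how many. A rule keyed to the proportions therefore looks at the wrong quantity. It can stay silent when selection differs between arms, and it can fire when nothing but chance is at work.

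Because the size of a qualifying imbalance is not fixed, someone decides whether the analysis is run after the data are seen. At stake is the credibility of one robustness check on the primary estimate, not the primary estimate itself.

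**Working it through.** **1. The plan's own figures.** From the Sample size section, the pooled SD is √((63² + 42²)/2) = √2866.5 = 53.5 minutes and d = 20/53.5 = 0.37. A two-sided two-sample t-test at α = 0.05 and 80% power needs 113.3, so 114 per arm. Attrition: 228/0.85 = 268.2, stated as 268 (134 per arm). These figures reproduce, and nothing below changes them.

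**2. Unequal proportions without bias.** The article does not state the share of women not reaching the active second stage, so I assume 10%, 15% and 19%. The last two are proxies only. The planned 15% attrition also covers dropout and some operative deliveries. The 19% is the hospital's primary caesarean rate (Setting), which may include second-stage caesareans, and those women do reach the stage. With the same true share p in both arms and n = 134 per arm, SE = √(2p(1−p)/134). The chances below are exact, from two independent binomials.

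| Assumed p | SE of difference | Gap above 5 points | Gap above 3 points |
|---|---|---|---|
| 10% | 3.7 points | 18% | 36% |
| 15% | 4.4 points | 27% | 44% |
| 19% | 4.8 points | 31% | 48% |

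The 3- and 5-point cut-offs are mine, because the article gives none. Read literally, any difference at all would occur in 92–94% of trials.

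**3. Equal proportions with bias.** Suppose that 85% reach the stage in both arms and there is no treatment effect. In one arm only, reaching depends on a predictor with latent correlation b, and that predictor has correlation r with duration. Among women reaching the stage in that arm, the predictor's mean shifts by b × φ(z)/0.85, where z = 1.036 is the 85th normal percentile and φ(z) = 0.233. The shift is therefore 0.274b, and the spurious difference is 0.274 × b × r × 53.5 minutes.

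- b = 0.3, r = 0.3: 1.3 minutes
- b = 0.5, r = 0.5: 3.7 minutes
- b = 0.7, r = 0.5: 5.1 minutes

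If selection runs in opposite directions in the two arms, these figures double, giving a range of 2.6 to 10.3 minutes. The difference that the trial is sized to detect is 20 minutes. The true proportions are equal throughout, so only a chance gap could fire the trigger. The correlations are assumptions, and the upper end needs the extreme opposite-direction case.

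**4. What the weights add.** With b = 0.6 and r = 0.5 in one arm, the unadjusted bias is 0.274 × 0.6 × 0.5 × 53.5 = 4.4 minutes. In a simulation with 134 per arm and linear effects, covariate adjustment alone reduced this to 0.1, and adding selection weights left it at 0.1. With an unmeasured predictor, about 4.1 minutes remained with or without weights. In simulations with a non-linear covariate effect or effect modification, weights removed a further 1.4 to 2.4 minutes after adjustment.

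**The case against.** The strongest reply is that little is lost when the trigger stays silent. The confirmatory model always adjusts for the covariates on which the weights would be built, and step 4 shows that adjustment does nearly all the work under linearity. The comparison of non-reaching women by standardised mean differences is unconditional and looks directly at composition. All of this stands, and it limits the size of the point. The one-arm bias in step 3 (1.3 to 5.1 minutes) is also below the standard error of the primary contrast, 53.5 × √(2/114) = 7.1 minutes.

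A trigger fired by chance does no harm beyond one more sensitivity analysis. The table in step 2 shows that the trigger discriminates poorly, not that it damages the result.

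A fuller analysis plan might define the threshold, so its absence from an article is not the complaint. The complaint is the condition itself, which the article fixes and which no threshold would repair.

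A reader might also infer that the sentence contradicts itself, because it confines weighting to data "applied to observations that are missing rather than undefined" and then weights for women whose duration is undefined. The text does not support that. The semicolon separates two differently named tools, one for missing records and one for selection into the stage. What remains is that the target of the second is not spelled out.

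**Conclusion.** The point holds as a minor improvement to a sensitivity analysis. An observed imbalance in proportions is neither necessary nor sufficient for selection bias. At identical true rates a gap above 5 points arises in about 18–31% of trials, assuming 10–19% do not reach the stage. Equal proportions can coexist with a bias of a few minutes under the assumed correlations.

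A reader might infer that the primary result is invalid or unprotected against selection. The documents do not support this. The confirmatory estimate, its interval and the type I error do not depend on the trigger, measured selection is largely handled by the adjusted model, and composition is reported in all cases. Neither adjustment nor weights on these covariates would correct unmeasured selection.

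**What to change.** 1. Delete the condition. Run the selection-weighted sensitivity analysis in all cases and report it beside the unchanged primary estimate.
2. Build the weight model from the baseline covariates of the primary model and their interactions with arm. Without the interactions it cannot represent selection that differs between arms.
3. State the target: the weights standardise the women who reached pushing to the baseline covariate mix of the randomised sample. They do not impute durations for women who never pushed, so the result should not be described as an effect on duration in all randomised women.
4. State that the analysis cannot correct selection on unmeasured factors.
5. Put it in its own sentence, apart from multiple imputation and weighting for missing partogram times or questionnaires.

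The cost is a few sentences, one extra model run and a slightly wider interval for that sensitivity estimate. Sample size, trial conduct and the confirmatory analysis do not change.
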